## Aims

The purpose of the proposal is two-fold: 1) to examine the effects of an IYP on IBS symptoms, global improvement, and quality of life in adolescents and young adults aged 14-26; and 2) to explore the mediating roles of physiological and psychospiritual processes through which IY is likely to impact outcomes.

The specific aims of the proposed project are:

1. To determine the safety, feasibility, and acceptability of the IYP in IBS patients aged 14-26 years.

2. To test for changes in clinical symptoms (primary outcomes), including self-reported IBS symptoms, global improvement, and health-related quality of life (HRQOL) immediately following a standardized IYP and at 2-month follow-up compared to usual care wait-list controls.

3. To assess changes in visceral sensitivity (assessed via a standardized laboratory visceral sensitivity task), disability and psychospiritual functioning (i.e., catastrophizing, mood, self-efficacy, acceptance, and mindfulness) (secondary outcomes) following the IYP compared to controls.

4. To explore potential mediators of clinical outcomes following the IYP, including psychospiritual functioning, visceral sensitivity, and ANS and HPA activity.

The hypotheses to be tested are:

1. The IYP will be safe, acceptable and feasible: at least 80% of subjects will complete the IYP.

2. Following the IYP, participants will demonstrate significantly greater improvement on the primary clinical outcomes of IBS symptoms, global improvement, and HRQOL relative to wait-list controls; gains will also be evident at the 2-month follow-up.

3. Following the IYP, participants will demonstrate significantly reduced visceral sensitivity and disability, and improved psychospiritual functioning, including coping, mood, self-efficacy, acceptance, and mindfulness (secondary outcomes) relative to wait-list controls.

4. Exploratory hypothesis: The impact of the IYP on the primary clinical outcomes will be mediated by improved psychospiritual functioning, reduced visceral sensitivity, and improvements in ANS and HPA dysregulation.

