## Primary outcomes

### Questionnaires at baseline, post-treatment, and follow-up

**1**. ***IBS symptoms ***will be measured using the ***IBS severity scoring system (IBS-SSS) ***[88]. The scale measures the sum of the participant's evaluation on a 100-point scale of each of five items: severity of abdominal pain, frequency of abdominal pain, severity of abdominal distension, dissatisfaction with bowel habits, and interference with quality of life. The IBS-SSS has acceptable reliability and validity and is recommended for use in outcome studies [89]. It takes approximately 5 minutes to complete. Those younger than 18 will also receive the abdominal symptoms sub-scale of the Child Somatization Inventory (CSI). The CSI [90-93] measures perceptions of nonspecific somatic symptoms. Individuals rate how much they are bothered by each of 24 symptoms (e.g., headaches) during the last 2 weeks using a 5-point scale (*not at all *to *a whole lot*). It takes less than 5 minutes to complete.

**2. *IBS pain ***will be measured with the ***Abdominal Pain Index ***comprising five items assessing the frequency, duration and intensity of pain episodes over the previous 2 weeks. Good reliability and validity have been reported [94].

**3**. ***Global Improvement ***will be assessed with the ***Global Improvement Scale **(**GIS**)*. This scale asks participants "Compared to the way you felt before you entered the study, have your IBS symptoms over the past 7 days been from (1) = substantially worse, to (7) = substantially improved [95]". Global improvement is noted for patients endorsing moderately or substantially improved status. The scale shows adequate reliability and validity [95]. Global improvement, in addition to symptom severity, is recommended as a primary endpoint in IBS therapy trials [96]. The scale takes less than 1 minute to complete.

**4**. ***Health Related Quality of Life ***will be assessed with the ***Health Related Quality of Life - Short Form-36 (SF-36) ***[97] a generic core HRQOL measure yielding an 8-scale profile of functional health and well-being. The SF-36 performs well in an absolute sense and comparatively better than other HRQOL measures in terms of reliability, validity, and lightness of respondent/administrative burden [98]. It can be completed in 5-10 minutes and has been validated in children as young as 10 years of age [99].

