To test **Hypothesis 4: **As depicted in Figure1, Psycho-spiritual-physiological outcomes will be explored as mediators of the association between IY and improved IBS outcomes. Regression analyses will be conducted to determine whether these variables mediate treatment outcome. The procedures outlined in Cohen and Cohen [124] will be used to calculate residualized change scores for IBS symptoms, global improvement, HRQOL and pain sensitivity scores. Multiple regression analysis will then be conducted with IBS symptoms, global improvement, and HRQOL separately; change scores (baseline minus post-treatment) will be regressed onto a set of predictor variables including group (yoga vs. control), the mediator variable of interest (e.g., self-efficacy), and the interaction between the mediator and group. If evidence of mediation is found using the traditional Baron and Kenny approach - the Sobel test - a statistical test for mediation will be conducted to calculate mediation. Finally, exploratory analyses will be conducted from the Weekly Monitoring data.

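### The mediation analysis names two different change scores for the same outcomes and does not define which indirect effect its Baron-Kenny and Sobel steps test once a mediator-by-group interaction is in the model

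*Protocol article*

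**What the plan says.** In the protocol article, under Data analyses, Hypothesis 4, the first step is to "calculate residualized change scores for IBS symptoms, global improvement, HRQOL and pain sensitivity scores". In the next sentence, for IBS symptoms, global improvement and HRQOL taken one at a time, "change scores (baseline minus post-treatment) will be regressed onto a set of predictor variables", these predictors "including group (yoga vs. control), the mediator variable of interest (e.g., self-efficacy), and the interaction between the mediator and group". The decision rule follows: "If evidence of mediation is found using the traditional Baron and Kenny approach - the Sobel test" is then run as the formal test.

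Two other places bear on this. Under Primary outcomes, the Global Improvement Scale asks patients to rate themselves "Compared to the way you felt before you entered the study", on a scale from 1 to 7. Under Aims, the fourth hypothesis is labelled as exploratory: "Exploratory hypothesis: The impact of the IYP on the primary clinical outcomes will be mediated by" psychospiritual, visceral and autonomic or hormonal change. Exploring mediators is nonetheless the second of the study's two stated purposes.

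**The concern.** Baron-Kenny and Sobel, in their usual form, assume one mediator-outcome slope shared by both arms. The planned regression lets the slope differ by arm. The analyst then has more than one candidate for path b and no instruction on which to put in the Sobel product. The interaction coefficient itself answers a different question, namely whether the slope differs between yoga and control.

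The outcome is also not fixed. A residualised change score and a baseline-minus-post difference are different variables, and for global improvement neither exists.

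At stake is whether the mechanism results can be interpreted. A null result would say little at this sample size, and a positive one would leave open which effect had been shown. No primary efficacy conclusion depends on it.

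**Working it through.** **1. The plan's own sample size.** The article gives a medium effect, correlations of .10 to .50, alpha .05 and power 0.80 for the pre/post by group interaction. It gives no number for the effect; f = 0.25 is assumed as the conventional medium value. With m = 2 time points, lambda = f² x N x m / (1 - rho), on 1 and N - 2 degrees of freedom:

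- rho .10, N = 60: 0.0625 x 60 x 2 / 0.90 = 8.33, power 0.810.
- rho .50, N = 34: 0.0625 x 34 x 2 / 0.50 = 8.50, power 0.807.
- Midpoint (60 + 34)/2 = 47; 47/0.80 = 58.75, so 59, against 60 stated.

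The stated figures reproduce. With 60 recruited and 20% lost, 60 x 0.80 = 48 remain, the size used below. None of this calculation concerns mediation.

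**2. Which outcome is regressed.** Residualised change is the post-treatment score minus its prediction from baseline. Raw change is baseline minus post-treatment. Both need a baseline score, which the global improvement rating does not have. For the other outcomes the choice was checked by simulation at N = 48 (a 0.8 SD effect of yoga on the mediator, b = 0.39, no interaction, Sobel test):

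| Pre/post correlation | Power, raw change | Power, residualised |
|---|---|---|
| .10 | 23% | 39% |
| .30 | 31% | 43% |
| .50 | 41% | 48% |

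The true indirect effect is 0.8 x 0.39 = 0.312. The mean estimate was 0.31 to 0.32 with raw change and about 0.30 with residualised change. The choice costs precision and has little effect on average bias.

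**3. What the interaction does.** Write the outcome as β0 + β1·G + β2·M + β3·G·M, with path a the effect of group on M. With G = 0 for control and 1 for yoga:

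- the mediator slope is β2 in controls and β2 + β3 under yoga;
- the indirect effects are a·β2 and a·(β2 + β3);
- β1 is the group effect at M = 0.

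Example: a = 0.5, with slopes 0.2 and 0.6. The product is 0.5 x 0.2 = 0.10, 0.5 x 0.6 = 0.30, or, with the average slope, 0.5 x 0.4 = 0.20. The article does not choose among them.

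Subtracting a constant from M changes β1 but leaves β2 as it was; the coding of G decides whether β2 is one arm's slope or the average of the two. With 0/1 coding, β2 rests on one arm, half the patients, so its standard error should rise by about √2 = 1.41. Simulation gives 1.43 to 1.44.

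**4. Power of the planned test.** Sobel's statistic is ab / √(a²·SE_b² + b²·SE_a²). N = 48; the article gives no path sizes, so all are assumed (a in SD units of the mediator, b standardised). Ranges cover repeated simulations with b of .39 or .40.

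| a, b | Sobel, no interaction | Sobel, uncentred 0/1 interaction | Percentile bootstrap, no interaction |
|---|---|---|---|
| 0.5, about .4 | 14-17% | 6-7% | 30-35% |
| 0.8, about .4 | 38-44% | 19-21% | 61-64% |
| 0.8, .59 | 71% | 54% | 80% |
| 1.0, .5 | 80% | 54% | 89% |

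With the group code centred, Sobel at a = 0.8, b = .39 is 40% with the interaction and 41% without. If the Baron-Kenny steps are taken to require a significant total effect, the full sequence with the 0/1 interaction reaches 14% at a = 0.8, b = .39 and a direct effect of 0.3, against 62% for the bootstrap.

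With no path a and b = .4, Sobel rejects about 1% and the bootstrap about 4%. At a = 0 and b = .8 the bootstrap rejects about 7%.

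**The case against.** Hypothesis 4 is exploratory, no power is claimed for it, and an article may leave coding and centring to a fuller plan. All of that stands and limits the weight of the point. The words in brackets after change scores may also be a loose way of naming the two time points, so raw change is not certain; the text still has to say which is meant.

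Several stronger readings are tempting, but the documents do not support them.

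- *The interaction makes the model unusable for mediation.* It does not. A treatment-by-mediator term is legitimate once arm-specific indirect effects are defined. The gap is that none is defined.
- *Path a is never estimated.* The Hypothesis 3 analyses of covariance compare the arms on visceral sensitivity and the psychospiritual variables, and Baron-Kenny includes the mediator-on-group step. Hypothesis 3 does not list the autonomic and cortisol mediators.
- *Moderation will be reported as mediation.* The decision rule is Baron-Kenny then Sobel, not the interaction coefficient, and Sobel is conservative when path a is absent.
- *The planned analysis halves power.* This depends on assumed paths and coding. It is about right for small-to-medium paths and too strong for large ones.
- *Raw change biases the indirect effect.* The check shows a loss of precision, not a material shift in the mean.
- *The group coefficient becomes useless.* Its SD rises from 0.27 to 0.92 only for an uncentred mediator with an assumed mean of 35 and SD of 12. It stays at 0.28 for a mean-zero mediator, and this coefficient does not enter the Sobel product.

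**Conclusion.** The point holds as a defect of specification with a secondary cost in power. Three parts rest on the text alone: two change scores are named for the same outcomes, one of those outcomes has no baseline for either, and the indirect effect under test is undefined once the interaction is in the model.

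The size of the power loss rests on assumed paths. At about 48 evaluable patients and small-to-medium paths, Sobel without the interaction finds the effect in about 14-44% of trials, against about 30-64% for a percentile bootstrap, and in about 6-21% with an uncentred 0/1 interaction. The shortfall narrows for large paths, and with centring the interaction adds almost nothing to it. The bootstrap also misses most smaller effects (65-70% at a = 0.5), so the change improves the analysis but does not make it well powered.

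The point is worth correcting because mediation is one of the two stated purposes and the repair is cheap.

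**What to change.** Replace the Hypothesis 4 analysis text with the following.

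1. For each mediator, regress the post-treatment mediator on group and baseline mediator. The group coefficient is a.
2. Regress the post-treatment outcome on group, post-treatment mediator, baseline mediator and baseline outcome, without the interaction. The mediator coefficient is b. For global improvement, use the rating itself and omit the outcome baseline.
3. Report a x b with a percentile bootstrap 95% confidence interval, resampling within arm, in place of the change scores, the Baron-Kenny gate and the Sobel test.
4. Examine the mediator-by-group interaction in a separate model, with the mediator centred and the group coding stated (centred if the mediator coefficient is to be the average slope). If the term is kept, report the indirect effect for each arm.

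The cost is revised wording, a bootstrap routine and a little more analysis work. The one statistical drawback is that the percentile bootstrap can run slightly above 5% type I error when one path is zero and the other large (about 7% at a = 0, b = .8). That is tolerable for an exploratory analysis and should be stated.

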#### Sample size determination and power analysis

Based on our previous pilot work using Iyengar yoga for patients with rheumatoid arthritis [82], we estimated that yoga was likely to have a medium effect size on the primary outcomes. For power calculations, a freely-available software for power calculations - G*Power 3- was used to estimate the sample size needed for the estimated effect size using a pre/post by group interaction. Pairing a medium effect size with a range of correlation values (.10 to .50) for baseline and follow-up scores resulted in power calculations ranging from 60 to 34 total subjects. These calculations used a Type I error rate of α = .05, and statistical power of 0.80 (the Type II error rate, 1- β). We settled upon the middle value of 47 total subjects. Assuming a 20% attrition rate, it was estimated that 60 total subjects would need to be recruited (30 per group).

### Protection of human subjects

This study was approved by the Medical Institutional Review Board 1 (MIRB1) within the Office of the Human Research Protection Program at UCLA (IRB Number 09-05-070-01). The study will be carried out in compliance with the Helsinki Declaration.

#### Risks to subjects

Yoga is generally regarded as safe and adverse effects are rare, especially within the Iyengar program in which props are used for support and teachers undergo vigorous training for certification. However, a number of case reports have indicated adverse events following yoga, specifically, the presence of subcutaneous emphysema [125] and shortness of breath and chest pain [126]. Nevertheless, these events were in response to intensive *pranayama*, or breathing exercises, with the shortness of breath case experiencing difficulty following *kapalabhati pranayama *involving strong forced breaths which may push the body to physiologic extremes [126]. Such intensive breathing techniques will not be used in this yoga intervention. Great care will be taken in developing the yoga program to ensure that bodily systems are not stressed.

The laboratory pain component of the study presents some potential risks to subjects. During physiological assessments, some subjects may be bothered by arm cuff inflation for blood pressure measurement. However, all participants should have had experience with these procedures from routine medical check-ups. Additionally, some physical discomfort may be experienced during the water load task. However, subjects are in control of how long the task takes--they may stop the procedure at any time and the experimenter will be in the room at all times to provide supervision and support. Also, the experimenter will discontinue the study if distress is observed in the subject whether or not the subject expresses distress. During the procedure, subjects may experience some potentially discomforting anxiety. However, the anxiety will be transitory and is unlikely to exceed levels of fearfulness that subjects experience naturally when unexpectedly encountering mild pain stimuli in their own environment. In past pain studies, we have not encountered any anxiety-related problems. Participants may also feel uncomfortable disclosing personal information about their mood and symptoms on study questionnaires.

### Protection against risk

#### Privacy and confidentiality

Confidentiality will be maintained by the use of unique identification numbers. All data, as well as participant lists, will be kept in locked file cabinets with access restricted to research staff. All data forms will have subject ID only.

#### Safety aspects of the study design and conduct

The major potential risks from the yoga class are strains or injuries. We will minimize these risks by conducting the yoga intervention in the safest manner possible. A progressive series of poses has been developed for this trial; this gradual progression, tailored to the participants, is designed to avoid injury. In addition, props will be used to support participants in more challenging poses. The general safety parameters of the yoga program are: 1) heart rate will not exceed moderate training range (115 BPM) - we will ask participants to check their pulse at the end of each yoga session during a timed one-minute period and to report their heart rate (anyone who remains at a rate of greater than 115 BPM will be interviewed and assessed by a physician to determine if this is a consistent finding or if there may be other isolated reasons for the tachycardia, such as a viral illness); 2) attention will be paid to spinal safety; 3) balance will be carefully monitored (e.g., chairs are used to assist balance as needed). Students will be given modifications of postures using props to accommodate for individual differences and limitations and receive individual attention if postures are too challenging.

To minimize potential risks or discomfort associated with the laboratory tasks, an experimenter will remain in the room for supervision and observation of subject responses. If subjects show signs of acute distress (e.g., tearfulness), the experimenter will stop the experiment and talk with the individual until he/she feels calmed. The patient can end the study participation or continue, depending upon how he/she feels. The team has developed ways of carrying out laboratory pain research with children to minimize threat and to make it an interesting and pleasantly novel experience.

To minimize any potential risks or discomfort associated with study assessments, all assessments will be conducted in a private room. Participants will be encouraged to raise questions or concerns at any time and be reminded that they may withdraw at any time without penalty. In addition, a clinical psychologist will train all research personnel to identify and report any history of abuse or risk for potential self- or other-harm if this information is revealed in responses to questionnaires or during interviews, as required by the study institution's IRB.

### Data and safety monitoring plan

The principal investigator will be responsible for maintaining quality control over the data collection process and for securing its confidentiality; she will oversee the process of data collection and ensure that data is reviewed for completeness and accuracy. Reviewed data will be secured in locked file cabinets in the project offices. During each of the treatment waves, potential threats to the safety and well-being of participants will be carefully monitored. If, for example, there is any adverse change in the medical condition of participants, the study physician will be immediately consulted and the participant's physician contacted to make arrangements for treatment, if necessary.

The proposed project is a single site study with low complexity and minimal toxicity risk. Nevertheless, a safety monitoring committee is appropriate for oversight of the research that includes safety officers who are IBS experts.

#### Monitoring process

Study performance and safety monitoring will be conducted. The list that follows shows the major items that will be included in the monitoring reports. The safety committee will receive bi-monthly summaries containing information on each item in the list, presented in a blinded manner. A trained research assistant will be in charge of preparing reports for the safety committee. In case of safety concerns (primarily about side effects), requests by the committee for unblinded information will be made to the study physican who will provide the necessary information.

#### Content of safety reports

The following performance and safety characteristics will be tabulated monthly and reported to the safety committee bi-monthly. Information on the date, time and nature of any adverse events will be reported separately for the yoga intervention and the visceral sensitivity task.

Performance summary:

1. Recruitment rates, including number of subjects who are screened, percent eligible at each stage of screening, reasons for non-eligibility, baseline visit rates, and randomization figures

2. Demographics of screened and enrolled participants by treatment group

3. Adherence of participants to study treatment (i.e., class attendance)

4. Percent of participants evaluated at each follow-up point and reasons for losses to follow-up

Safety summary:

Iyengar yoga intervention

1. Worsening of symptoms, as documented by the weekly monitoring form

2. Possible side effects, including any cardiovascular event during class

3. Injuries occurring in class or during home practice

4. Any other unrelated, possibly related, and related adverse events by subject

5. Attribution of adverse event to the study intervention, determination of whether the adverse event was expected or unexpected, and study adjustments as necessary

Laboratory visceral sensitivity task

1. Possible side effects, including any cardiovascular event

2. New pain that persists by the end of the lab session

3. Any other unrelated, possibly related, and related adverse events by subject

4. Attribution of adverse event to the study intervention, determination of whether the adverse event was expected or unexpected, and study adjustments as necessary

